### Sample size calculation

Based on previous study which explored the efficacy of renal sympathetic denervation in treating hypertension, we assume that for the current study the primary outcome (the change of 24 h ABPM systolic blood pressure from pre-operation to the measurement at 3 months post-operation) has a standard deviation of 15 mm Hg [14]. We wish to be able to detect a difference of 11 mm Hg. Assuming a 20 % drop-out rate, a total of 50 participants are required to provide 90 % power, with the risk of two-sided type І error of 0.01.

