#### Withdrawal of individual subjects

Subjects can withdraw from the study at any time for any reason without any consequences. The investigator can also decide to release a subject from the study for medical reasons. For every subject who decides to withdraw from the study, the reasons for withdrawal will be recorded.

A total of 18 patients have given informed consent for participation and been enrolled into the study from July 2014 to Oct 2015.

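### The stated sample size does not follow from its own inputs: they require about 40 enrolled patients, not 50, and 50 enrolled give about 97% power rather than 90%

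*Protocol article*

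**What the plan says.** The Sample size calculation section of the protocol article gives all the inputs that a one-group calculation needs.

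- Outcome: "the change of 24 h ABPM systolic blood pressure from pre-operation to the measurement at 3 months post-operation", which is a within-patient change.
- Variability: this change "has a standard deviation of 15 mm Hg", a value taken from a study of renal sympathetic denervation.
- Effect: "We wish to be able to detect a difference of 11 mm Hg".
- Attrition: "Assuming a 20 % drop-out rate".
- Error rates: 90% power "with the risk of two-sided type" I error of 0.01.

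From these it concludes that "a total of 50 participants are required to provide" that power. No formula or test is named. Study design and Setting describes one cohort with no control group. Study endpoints and Statistical analysis compare the second measurement with both the third and the fourth (1 and 3 months after surgery), using analysis of covariance.

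**The concern.** The standard deviation is given for the change itself, and there is one group. No correlation, allocation ratio or variance therefore has to be guessed, and the stated size should be reproducible from the section alone. It is not. The inputs lead to a number well below 50, so either the requirement of 50 or the power of 90% is wrong as written, or an allowance was made that the text does not mention.

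What is at stake is the accuracy of the main planning figure. A reader or ethics board is told that 50 is the minimum for 90% power. On the stated inputs it is not the minimum, and the power at 50 is understated. A reader also cannot tell how much margin the study has if the standard deviation is larger, or the effect smaller, than assumed.

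**Working it through.** **Inputs** (all from Sample size calculation; the single group is from Study design and Setting): SD of the change 15 mm Hg; difference 11 mm Hg; two-sided alpha 0.01; power 0.90; drop-out 0.20. Standardised difference = 11/15 = 0.733.

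**Attempt to reproduce 50 from the stated inputs**

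1. Normal approximation: n = (z for 1 − alpha/2 + z for power)² × (SD/difference)² = (2.576 + 1.282)² × (15/11)² = 27.7, so 28 evaluable. Enrolled: 28/0.8 = 35.
2. One-sample t on the change, exact power from the noncentral t distribution with n − 1 degrees of freedom and noncentrality 0.733 × √n:
   - n = 31: power 0.899, just short of 0.90
   - n = 32: power 0.911, so 32 evaluable
   - Enrolled: 32/0.8 = 40
3. Inflating by 1.2 instead of dividing by 0.8 gives 34 (normal) or 39 (t).

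None of these is 50. The excess over the t-based figure is 50 − 40 = 10 patients, or 10/40 = 25%.

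**What 50 enrolled provides**

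Evaluable patients: 50 × 0.8 = 40. Noncentrality = 0.733 × √40 = 4.64, which gives power 0.969 (0.980 by the normal approximation). With 40 evaluable and power held at 90%:

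- the detectable difference is about 9.6 mm Hg if the SD is 15; or
- an SD of about 17.3 is tolerated if the difference is 11.

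**Readings that change one or more inputs** (noncentral t unless noted)

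| Reading | Evaluable | Enrolled |
|---|---|---|
| Alpha 0.005 (two time points), 90% power | 36 | 45 |
| Alpha 0.01, 95% power | 37 | 47 |
| Alpha 0.005 and 95% power | 41 | 52 |
| SD 17 instead of 15 | 39 | 49 |
| Signed-rank test at worst-case efficiency 0.864 | 38 | 48 |
| 20% drop-out applied twice | 32 | 50 |
| Two-sample formula, alpha 0.05, 90% power (per arm) | 40 | 50 |
| SD 15 read as the SD of one measurement, pre/post correlation 0.3 | 43 | 54 |
| The same, correlation 0.4 | 37 | 47 |

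Several of these come to 50 or close to it. Each departs from something the section states or adds something it does not state.

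**The case against.** The best defence is that the discrepancy is on the safe side and that 50 is a sensible number for this study. The primary endpoint uses two post-operative time points, while the calculation sizes only the 3-month change. Splitting alpha across the two takes the requirement to 45, and also asking for 95% power takes it to 52. The standard deviation comes from a different intervention, and at 17 mm Hg the same calculation gives 49. Participants are already scheduled for the surgery, so a larger sample adds only ambulatory recordings and follow-up visits. All of this stands as a reason to keep 50. It does not rescue the sentence, which mentions none of these allowances and presents 50 as what the listed inputs require for 90% power.

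Three stronger readings are tempting, and the document does not support them.

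- **How 50 arose.** Applying the drop-out twice reproduces it exactly (32/0.8 = 40, then 40/0.8 = 50), but so does a two-sample formula at alpha 0.05. The text does not let one choose between these or exclude another cause.
- **That the surplus is a costly recruitment delay.** The article reports that "A total of 18 patients have given informed consent for participation and been enrolled into the study from July 2014 to Oct 2015". It also says that about 30–40 patients with both conditions are seen each year, but that describes the source pool before exclusions and consent. No expected enrolment rate is stated, so a shortfall against one cannot be shown. Nor is a slow pace a reason for a lower target.
- **That the analysis should be named as a paired t-test at 3 months.** The t calculation here only checks the size. The planned analysis is analysis of covariance with both post-operative measurements.

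**Conclusion.** The statement is wrong as written. On its own inputs the requirement is 32 evaluable and 40 enrolled patients (28 and 35 by the normal approximation), not 50. Fifty enrolled with 40 evaluable give about 97% power, not 90%. This rests on taking the section at its word: 15 mm Hg is the SD of the within-patient change, there is one group, a single 3-month comparison is tested at two-sided alpha 0.01, and 20% of patients are lost.

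A reader who sees a failed sample size calculation might infer that the study is underpowered. The opposite holds: on these inputs it is oversized. The consequence is a planning figure that cannot be traced and an understated power, with no threat to the primary comparison.

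**What to change.** Rewrite the concluding sentence of Sample size calculation in one of these ways.

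- Keep 50 and state what it provides: about 97% power for 11 mm Hg with 40 evaluable patients; equivalently, 90% power for about 9.6 mm Hg, or for 11 mm Hg if the SD is about 17.3 mm Hg.
- Keep 50 and state the formula with the extra allowance that leads to it, for example for the two post-operative time points or for uncertainty in the borrowed SD.
- Restate the requirement as 32 evaluable and 40 enrolled for the single 3-month comparison. This gives up the margin that 50 provides for the second time point and for a larger SD.

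Either of the first two keeps the design as it is. The cost is one corrected sentence; no extra patients are needed and the planned analysis does not change.

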### Statistical analysis

Analyses will be made using SAS statistical software (version 9.3) by researchers at the Peking University Clinical Research Institute. The change in systolic ABPMs over the four times will be analyzed to observe the overall pattern of the blood pressure change in relation to the surgery, but the primary analysis will be the comparison of systolic ABPM between the 2^nd^ and 3^rd^, 4^th^ measurements (before and after the surgery). We will also calculate the regression-to-the-mean adjusted changes in systolic ABPMs as sensitivity analysis. Primary endpoint analyses and the change in systolic ABPMs over the four times will be carried out using analysis of covariance, as well as the first secondary endpoint (the change of 24 h ABPM diastolic blood pressure). Descriptive statistics will be used to summarize control status of blood pressure, the use and dose adjustment of antihypertensive medication and the incidence of operative complications.

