**Methods/Design:**

The study will be a time series cohort study. Fifty eligible patients will be selected consecutively from the Peking University First Hospital. Two 24-h ambulatory blood pressure measurement (ABPM) will be taken before the surgery, apart by at least 3 days. The patients will be followed up for another two ABPMs at 1 and 3 months after the surgery.

We will recruit subjects with cervical spondylosis myelopathy meeting operation indications and scheduled for receiving cervical decompressive surgery, aged 18–84 years, have a history of hypertension or office systolic blood pressure ≥140 mmHg on initial screening, and willing to participate in the study and provide informed consent. Exclusion criteria includes a history of known secondary hypertension, visual analogue scale (VAS) score ≥4, and unable to comply with study due to severe psychosis.

The change in systolic ABPs over the four times will be analyzed to observe the overall pattern of the blood pressure change in relation to the surgery, but the primary analysis will be the comparison of systolic ABP between the 2^nd^ and 3^rd^ , 4^th^ measurements (before and after the surgery). We will also calculate the regression-to-the-mean adjusted changes in systolic ABP as sensitivity analysis. Secondary endpoints are the changes in 24 h ABPM diastolic blood pressure, blood pressure control status, the use and dose adjustment of antihypertensive medication, and the incidence of operative complications. Primary outcome analyses will be carried out using analysis of covariance, as well as the first secondary endpoint.

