## Methods and design

### Study design and Setting

The study is a time series cohort study. Patients with both cervical spondylosis myelopathy and hypertension are invited to participate in the study and subsequently receive cervical decompressive surgery. Patients are recruited continuously by surgeons at the Department of Orthopaedics, Peking University First Hospital in which there are about 30–40 patients with both cervical spondylosis myelopathy and hypertension each year. These subjects will be followed up at 1 and 3 months post-operation after enrollment. The study procedures and informed consent form have been approved by the Institutional Review Boards of the Peking University Health Science Center in Beijing, China, and registered at NCT02016768. Figure 1 shows an overview of the most important procedures in the study.

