### Study endpoints

The primary endpoint is estimated as the difference between systolic ABPM before surgery (2^nd^ measurement) and the systolic ABPM at 1 month and 3 month post-operation (3^rd^ and 4^th^ measurement).

Four secondary endpoints were defined as: 1) The difference between diastolic ABPM before surgery and ABPM diastolic blood pressure at 1 month and 3 month post-operation; 2) control status of blood pressure at 1 month and 3 month post-operation (blood pressure control is achieved if systolic/diastolic blood pressure <140/90 mm Hg, reducing systolic blood pressure by >20 mm Hg or reducing diastolic blood pressure >5 mm Hg); 3) the use and dose adjustment of antihypertensive medication; and 4) the incidence of operative complications, including spinal nerve trauma, incision infection and fluid, pneumonia and urinary system infection etc.

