Through long–term clinical observations, we have found that high blood pressure or fluctuated blood pressure among many patients decreased substantially or became stable post-operatively. Therefore, we infer that cervical decompressive surgery may be a novel alternative in treating hypertension and will effectively reduce blood pressure in patients with cervicogenic hypertension. Therefore, a substantial number of patients with both hypertension and cervical spondylosis may benefit from this approach as the decrease in the quantity and/or dose of antihypertensive drugs would subsequently lead to fewer side effects from them. Regarding the rationale for the reduction on blood pressure, we speculate that the compression or irritation of the dura mater and the posterior longitudinal ligament of the cervical spine may increase the sympathetic nervous activation. This discharge may pass through the ganglia and the sympathetic trunk to the postganglia fibers arriving at the target organ, such as the vertebral artery and the blood vessels and subsequently induce hypertension. Decompressive cervical surgery, either anterior cervical discectomy and fusion or posterior laminoplasty, may withdraw any compression of the dura and the posterior longitudinal ligament and thus the sympathetic irritation will be relieved leading to a decrease of blood pressure.

Our study has a number of limitations. This is not a randomized controlled clinical trial, factors such as placebo and Hawthorne effects cannot be ruled out entirely. However, we tried to measure blood pressure two times both before and after the surgery, these multiple measurements would help to better understand if the change in blood pressure is attributed to the surgery or purely to the regression to the mean. Although the randomized controlled trial is the gold standard study design, it is unethical to conduct such a trial considering the inappropriateness of treating hypertension with a cervical decompressive surgery. In our opinion, the study still gains important scientific information. Once our hypothesis is approved, it will provide an innovative mechanism of hypertension development, which may lead to the development of new methods of hypertension treatment and prevention.

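### Analysis of covariance is named for a one-group before/after change; with the pre-operative value as covariate it either does not test the mean change or understates its standard error

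*Protocol article*

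**What the plan says.** The design is a single cohort. Study design and Setting states: "The study is a time series cohort study". The Discussion concedes: "This is not a randomized controlled clinical trial".

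The endpoint is a within-patient change. Study endpoints says: "The primary endpoint is estimated as the difference between systolic ABPM before surgery" (2nd measurement) and the values at 1 and 3 months (3rd and 4th measurements).

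Sample size calculation is built on that change. Its outcome, the change from pre-operation to 3 months, "has a standard deviation of 15 mm Hg", and the target is stated as "We wish to be able to detect a difference of 11 mm Hg". The section adds 20% drop-out, 90% power and a two-sided type I error of 0.01, and arrives at 50 participants.

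Statistical analysis then assigns the method: "Primary endpoint analyses and the change in systolic ABPMs over the four times will be carried out using analysis of covariance", and extends it to the change in diastolic ABPM. The abstract (Methods/Design) repeats the choice: "Primary outcome analyses will be carried out using analysis of covariance, as well as the first secondary endpoint". Neither place names a factor, a covariate, a paired test or a model for within-patient correlation. An adjustment for regression to the mean is listed separately, as a sensitivity analysis.

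**The concern.** Analysis of covariance usually compares the levels of a factor after adjustment for a covariate, most often groups adjusted for baseline. Here there is no second group, and the question is whether one mean change differs from zero. If the usual habit is followed and the pre-operative ABPM becomes the covariate, the output contains no term that answers that question with the right standard error.

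Without a control group, the before/after test carries the whole primary claim, and the sponsor chose a strict level of 0.01 for it. A method that does not hold that level, or one that gives away power, affects the main result. The same choice is carried over to the first secondary endpoint.

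**Working it through.** **Inputs from the protocol article (Sample size calculation).** SD of change 15 mm Hg; difference 11 mm Hg; two-sided alpha 0.01; power 90%; drop-out 20%, so 50 × 0.8 = 40 evaluable.

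**Assumptions.** The documents give no correlation between two ABPMs in one patient. I take rho from 0.3 to 0.9, equal between all visits, with equal variances and normal data. The checks use the 3-month change.

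**The plan's own figure.** A paired test needs n = (15 × (2.576 + 1.282) / 11)² = 27.7, so 28 evaluable and 28/0.8 = 35 enrolled. With the t distribution it is 32 evaluable and 40 enrolled. The stated 50 is not reproduced; it is larger than needed, which is a separate matter. With 40 evaluable the paired t-test has 96.9% power, and its standard error is 15/√40 = 2.37 mm Hg.

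**Form A: change regressed on the 2nd ABPM.**

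1. A visit effect fitted to the post-operative values compares month 1 with month 3, not before with after.
2. The intercept with uncentred baseline is the predicted change at a pressure of 0 mm Hg. In simulation with no true change (n = 40, assumed mean 140 mm Hg) it rejects at nominal 0.01 in 95%, 77% and 46% of trials at rho 0.3, 0.5 and 0.7.
3. The intercept at the mean baseline equals the raw mean change, but its standard error uses the residual variance. Let σ² be the variance of a single ABPM. The change has variance 2σ²(1−rho), and the residual has σ²(1−rho²). The standard error ratio is √[(1−rho²)/(2(1−rho))] = √((1+rho)/2).

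The critical value on 38 degrees of freedom is 2.712. For the unconditional mean change, the true type I error is P(|t₃₈| > 2.712 × ratio):

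| rho | ratio | SE (mm Hg), correct 2.37 | 2.712 × ratio | true alpha at nominal 0.01 |
|---|---|---|---|---|
| 0.3 | 0.806 | 1.91 | 2.19 | 0.035 |
| 0.5 | 0.866 | 2.05 | 2.35 | 0.024 |
| 0.7 | 0.922 | 2.19 | 2.50 | 0.017 |
| 0.9 | 0.975 | 2.31 | 2.64 | 0.012 |

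Simulation agrees: 0.032 to 0.034, 0.023 to 0.024 and 0.015 to 0.017 at rho 0.3, 0.5 and 0.7. The paired t-test stays at about 0.01 throughout.

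With the SD of change held at 15, the SD of a single ABPM is 15/√(2(1−rho)). That is 12.7 mm Hg at rho 0.3, 19.4 at 0.7 and 33.5 at 0.9.

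4. For the course over four visits, the 2nd ABPM would be both an outcome and the covariate.

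**Form B: visit as factor, pairing ignored.** The standard error is too large by 1/√(1−rho): 1.41 at rho 0.5 and 1.83 at rho 0.7. Simulated type I error is below 0.001. Simulated power for 11 mm Hg is 81% and 45%, against about 97% for the paired test.

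**Form C: change adjusted only for the centred 1st ABPM.** Simulated type I error is 0.010 to 0.011, so this form is valid. So is a model with visit as factor that represents the within-patient correlation.

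**The case against.** The strongest reply is that no sentence makes the 2nd ABPM the covariate. Analysis of covariance is a linear model with a factor and covariates, and the factor could be visit. The same sentence covers the course over four visits, which favours that reading. Covariates, centring and covariance structure are details that an article may leave to a fuller plan. The understated standard error is also valid conditional on the observed baselines. And at the planned effect the paired statistic is 11/2.37 = 4.6, so a standard error 3% to 19% too small would seldom change the conclusion there.

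Most of this stands, and it limits the point. A reader might infer that the named method must be meaningless or anti-conservative; the text does not support that, because valid and conservative forms fit the same words. A reader might also infer that an intercept at 0 mm Hg would be reported as the effect, or that patients who miss one post-operative ABPM would be dropped. The article says neither.

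What does not stand is the claim that only detail is missing. The article makes a positive choice of method, twice, and the customary form of that method does not suit the endpoint. The endpoint is the mean change itself, so the unconditional standard error is the relevant one. Type I error concerns the case of no effect, so a large planned effect does not answer it.

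**Conclusion.** The point holds in limited form. The named method does not fix a test of mean change equal to zero. In its customary form, with the pre-operative ABPM as covariate, it either tests something else or has a type I error of about 0.035 to 0.012 instead of 0.01, for rho from 0.3 to 0.9 and 40 evaluable patients. The inflation is modest if rho is high. If pairing is ignored, the error runs the other way, with power of about 81% or 45% at rho 0.5 or 0.7.

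These sizes rest on an assumed rho, equal variances and correlations across visits, and the article's SD of change of 15 mm Hg. The documents do not show which form will be fitted, so this is not proof that the primary p-value will be wrong.

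Sizing on the SD of a change does not by itself contradict a covariate-adjusted analysis. It does show that the paired change is the quantity the trial was sized to test.

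**What to change.** In Statistical analysis and in the abstract, replace analysis of covariance, for systolic and diastolic ABPM, by a repeated-measures mixed model on all four ABPMs. Use visit as a four-level factor, model the within-patient covariance (for example unstructured), and do not use the 2nd ABPM as a covariate. Test visit 3 minus visit 2 and visit 4 minus visit 2 from that model, and give the paired t-test as a check.

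State which contrast is primary. Visit 4 minus visit 2 matches the outcome in Sample size calculation, but Study endpoints and Statistical analysis name both the 3rd and 4th measurements. Either identify the 3-month contrast as primary or reconcile the sections; the model alone does not settle this.

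The cost is one sentence in each place and a few lines of code. Compared with the baseline-adjusted interval, the correct one is wider by a factor of 1/0.975 = 1.03 (rho 0.9) to 1/0.806 = 1.24 (rho 0.3). No extra patients are needed, since 40 evaluable give about 97% power for the paired 3-month change.

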## Discussion

The etiology and mechanism of essential hypertension remains unclear. Non-operative methods of essential hypertension treatment including antihypertensive pharmacologic drugs are still unsatisfactory [5, 8]. In the past several years, a new procedure named renal denervation had been shown to be safe and effective in controlling hypertension, supporting that the sympathetic nervous system (SNS) activity is critical in regulating blood pressure [6, 7]. Recently, we have proposed a novel hypothesis that cervical spondylotic myelopathy may be an important etiology of essential hypertension which has been termed as cervicogenic hypertension [13]. In our previous study, we found that the high blood pressure in 12 out of 30 (40 %) hypertensive patients was reduced to normal levels following the cervical decompressive surgery, which resulted in a termination of the antihypertensive medications. Furthermore, the high and unstable blood pressure in the other 15 patients became stabilized and was well controlled by antihypertensive drugs after cervical decompressive surgery [13]. Recently, Peng et al. reported two cases of cervical spondylosis with hypertension [15]. After anterior cervical discectomy and fusion, the blood pressure of both the two patients remain normal without hypertensive medications [15]. Also, we speculate that renal denervation only destructs the network of SNS, and that the diseased cervical SNS has a greater impact on initiating and increasing SNS activity, as it may be closer to central nervous system than the normal renal SNS.

Through long–term clinical observations, we have found that high blood pressure or fluctuated blood pressure among many patients decreased substantially or became stable post-operatively. Therefore, we infer that cervical decompressive surgery may be a novel alternative in treating hypertension and will effectively reduce blood pressure in patients with cervicogenic hypertension. Therefore, a substantial number of patients with both hypertension and cervical spondylosis may benefit from this approach as the decrease in the quantity and/or dose of antihypertensive drugs would subsequently lead to fewer side effects from them. Regarding the rationale for the reduction on blood pressure, we speculate that the compression or irritation of the dura mater and the posterior longitudinal ligament of the cervical spine may increase the sympathetic nervous activation. This discharge may pass through the ganglia and the sympathetic trunk to the postganglia fibers arriving at the target organ, such as the vertebral artery and the blood vessels and subsequently induce hypertension. Decompressive cervical surgery, either anterior cervical discectomy and fusion or posterior laminoplasty, may withdraw any compression of the dura and the posterior longitudinal ligament and thus the sympathetic irritation will be relieved leading to a decrease of blood pressure.

Our study has a number of limitations. This is not a randomized controlled clinical trial, factors such as placebo and Hawthorne effects cannot be ruled out entirely. However, we tried to measure blood pressure two times both before and after the surgery, these multiple measurements would help to better understand if the change in blood pressure is attributed to the surgery or purely to the regression to the mean. Although the randomized controlled trial is the gold standard study design, it is unethical to conduct such a trial considering the inappropriateness of treating hypertension with a cervical decompressive surgery. In our opinion, the study still gains important scientific information. Once our hypothesis is approved, it will provide an innovative mechanism of hypertension development, which may lead to the development of new methods of hypertension treatment and prevention.
